#### Handling of missing data

Missing data may compromise findings from randomised clinical trials, particularly if missingness is not at random (MAR) and if missing data are not handled appropriately [80]. We will follow recommendations in the paper by Jakobsen et al. to handle missing data. This may include best-worst and worst-best sensitivity analyses, and full information maximum likelihood [80]. In the case of single missing observations on the three subscales of ATMS-S, person measures (subscale units per person) will be calculated using anchored item difficulty and category structure in a Rasch analysis. Winsteps software (updated version) will be used for Rasch analyses.

### Health economic evaluation

The health economic evaluation will be based on a societal perspective and use the change in QALYs as the main outcome variable. Based on the change in QALYs, the cost per QALY will be calculated by the incremental cost-effectiveness ratio (ICER) as follows:

$$ \mathrm{ICER}=\frac{C_i-{C}_j}{e_i-{e}_j}, $$

where *c*_*i*_ and *e*_*i*_ are the cost and effect for the intervention group and *c*_*j*_ and *e*_*j*_ are the cost and effect for the control group. The cost included here is the cost for the interventions (LGO-S and TAU), which will be estimated based on the information provided by the interventionist regarding the activities that are performed and the time that it takes to perform them. The cost measure will include both direct costs, such as the materials that are used, and time-use costs. For LGO-S, this will also include the cost of the 2-day training that the interventionists are required to attend. There will be no access to other health or social care costs.

Apart from calculating the ICER based on the QALYs gained, we will also incorporate a cost-effectiveness analysis using self-reported time management skills as measured with the ATMS-S as the main outcome.

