#### Cost-effectiveness measure

To enable a cost-utility analysis, we will measure health-related quality of life using the EQ-5D-5L, developed by EuroQol [74]. In the EQ-5D-5L, the individual’s health status is measured in the five dimensions of mobility, self-care, usual activities, pain/discomfort, and anxiety/depression using a 5-level scale ranging from no problem to extreme problems. By using a value set, this can be converted to a health index ranging from 0 (dead) to 1 (perfect health). A Swedish value set is currently under development and if available will be used when analysing the data. By multiplying the change in health-related quality of life by the duration of this change, expressed in years, the result will be the change in quality-adjusted life years (QALYs), which is the outcome most commonly used in health economic evaluations.

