When including an intervention such as TAU in a study, one foreseen challenge is the individual intervention design, involving both strategy building and prescription of time-assistive devices. While there is research evaluating time-assistive devices, the whole intervention package with all its variations has not yet been studied. Nevertheless, this is the nature, and the beauty, of clinical occupational therapy, and as such, it needs to be included in trials. In this trial, we will need to compensate for the vague and general description of TAU beforehand by providing more detailed descriptions of the method when reporting on the trial results. A limitation of this trial is the lack of blinding to group allocation by assessors and interventionists. The outcomes in this trial are however mostly self-report measures and they are therefore more prone to participant bias and only secondarily to assessor bias. Participant bias is subject to potential response shift, i.e. that increased awareness will make the participants more strict in their self-assessment after intervention than before. In that case, the effect of intervention would be underestimated. This possible response shift could however occur in both treatment arms and the effect on between-group differences might be less affected. Another limitation in this trial is the lack of public involvement in the design, planning, and execution of the trial. The health economic evaluation will be limited by the lack of access to general health and social care costs over and above the costs of interventions.

This trial has the advantage of being carried out in close collaboration with the clinics in the trial, and the implementation of the intervention is included in the trial design. This means that if LGO-S is proven to be an effective intervention, there are forms for implementation in place for further use in clinical settings.

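### The economic evaluation is labelled societal, but the only costs it counts are those of delivering the two interventions

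*Protocol article*

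**What the plan says.** The Health economic evaluation section opens with the perspective: "The health economic evaluation will be based on a societal perspective and use the change in QALYs as the main outcome variable". It then limits the numerator of the ICER to the cost of the two interventions, "which will be estimated based on the information provided by the interventionist regarding the activities that are performed and the time that it takes to" carry them out. On components it says: "The cost measure will include both direct costs, such as the materials that are used, and time-use costs". One item is added for one arm: "For LGO-S, this will also include the cost of the 2-day training that the interventionists are required to attend". The paragraph closes with: "There will be no access to other health or social care costs".

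The Discussion returns to this as a limitation: "The health economic evaluation will be limited by the lack of access to general health and social care costs" beyond those of the interventions. It does not mention the perspective again.

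Cost-effectiveness is the fourth hypothesis under Objectives, covering both quality of life and time management. The Discussion says the trial will show whether LGO-S is cost-effective for time management, with no qualification there about whose costs are meant. A second ratio, with the ATMS-S time management score as effect, is also planned and would presumably use the same costs.

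**The concern.** A societal perspective counts costs whoever bears them: the care provider, other parts of health and social care, the participant, the family and the employer. The plan counts what it costs to deliver LGO-S and TAU and nothing further. It thus claims a property that its own cost list does not have, within one section.

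At stake is how the fourth hypothesis is read. A ratio published as societal would be taken to include costs that were never collected. Participant time needs separate attention, because the arms differ in how they use it. A group session uses two leaders for six to eight attenders, whereas an individual visit normally pairs one therapist with one participant. An analysis that values only staff time and one that values both can therefore order the arms differently.

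**Working it through.** **Step 1. Cost categories set against the plan.** The economic section states no cost, utility or ratio, so there is no figure to reproduce. The check is a comparison.

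| Cost category | Status in the protocol article |
|---|---|
| Staff time delivering LGO-S and TAU | Counted |
| Materials | Counted |
| LGO-S leader training | Counted |
| Participant time in sessions | Unclear: time-use costs are not defined, and the stated source is the interventionist |
| Other health and social care | Expressly unavailable |
| Productivity, travel, informal care | Not listed |

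The first three rows are intervention costs. Even if the fourth were counted, the last two would keep the result from being societal.

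**Step 2. What the recorded data could support.** Under Trial-specific forms, the interventionist records the number of sessions and which ones were attended (LGO-S), and the number of sessions and the duration of each (TAU). LGO-S sessions are nominally 1.5 h (Interventions). Participant hours can therefore be derived in both arms. Work information is listed only on the pre-intervention form, so the text gives no basis for costing productivity changes.

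**Step 3. Hours per participant.** Inputs from the Interventions section: 10 sessions, 1.5 h each, two leaders, six to eight participants per group.

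- LGO-S leader contact hours per group: 2 × 10 × 1.5 = 30. Per participant: 30/8 = 3.75 to 30/6 = 5.0.
- LGO-S participant hours at full attendance: 10 × 1.5 = 15. At 7 sessions, the article's threshold for a programme completer: 7 × 1.5 = 10.5.
- TAU contact hours: not given. The article says the number of visits and the duration are not standardised. Call this *t*, and assume one therapist per participant, so that staff and participant hours are both *t*.

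The difference in participant hours, LGO-S minus TAU, is 15 − *t* at full attendance. It is positive for *t* below 15 and negative above. At 7 sessions attended the dividing point is 10.5.

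**Step 4. Effect on the ordering of the arms.** Value a participant hour at *w* staff hours (assumed) and count contact time only. LGO-S costs *s* + 15*w*, with *s* from 3.75 to 5, and TAU costs *t*(1 + *w*). The arms break even at *t* = (*s* + 15*w*)/(1 + *w*).

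| *w* | Break-even TAU hours |
|---|---|
| 0 (staff time only) | 3.75 to 5.0 |
| 0.5 | 11.25/1.5 = 7.5 to 12.5/1.5 = 8.3 |
| 1 | 18.75/2 = 9.4 to 20/2 = 10.0 |

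LGO-S is the cheaper arm above the break-even point. With *w* = 1 and TAU between 5 and about 9.4 h, staff time alone makes LGO-S cheaper, while staff plus participant time makes it dearer, at any permitted group size. Below 3.75 h or above 10 h the two views agree on the sign. Materials, devices, training and preparation are left out, so this shows sensitivity and is not an estimate.

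**The case against.** The best defence is disclosure. The paragraph that uses the label also sets out which costs are counted and says others are unavailable, and the Discussion repeats the limitation. The word societal appears once, in a secondary analysis, and a careful reader can see what the ratio contains. Time-use costs are not confined to staff and may include participant time. All of this is fair, and it keeps the point modest. It does not remove the contradiction: the article is not silent on the perspective but names one, and the Discussion's limitation covers health and social care costs only.

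Three stronger readings are tempting and are not supported.

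- *The omission favours LGO-S.* This depends on TAU hours, which the article leaves open. Above 15 participant hours in TAU, leaving out participant time would work against LGO-S. Participant time may also already be counted.
- *The QALY rule over-counts gains that build up gradually.* The Cost-effectiveness measure section says: "By multiplying the change in health-related quality of life by the duration of this change". This is a general definition that does not fix which change or which interval is used, and area under the curve is compatible with it. Assume visits at weeks 0, 13 and 24.5 and a unit gain that rises linearly to week 13 and is then held. The area is 13/2 + 11.5 = 18 weeks. The final change over the whole period gives 24.5 (ratio 1.36); over the last interval only, it gives 11.5 (ratio 0.64). If the gain rises linearly to week 24.5, the whole-period reading gives 24.5/12.25 = 2.0. Neither the direction nor the size is a property of the plan.
- *A societal cost-per-QALY conclusion is already claimed.* The article contains only a hypothesis and a promise to report, and neither uses the word societal.

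**Conclusion.** The point holds as a mismatch between the declared perspective and the costs collected. The planned ratio is an intervention-cost ICER, and nothing described in the article would make it societal. This rests on the text alone and needs no assumption.

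The monetary size cannot be given, since the article states no unit costs and no TAU hours. Whether participant time would change the ordering of the arms is open: under the Step 4 assumptions it does for TAU of about 5 to 9.4 h when the two kinds of hour are valued equally. The matter affects one of four hypotheses and leaves the primary endpoint alone.

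**What to change.** 1. In the Health economic evaluation section, restate the perspective as intervention-cost (provider), and word the cost-effectiveness conclusion accordingly for both the QALY and the ATMS-S ratio.
2. State whether time-use costs include participant time. If they do not, add a secondary result that does: sessions attended × 1.5 h for LGO-S, and session number × recorded duration for TAU, with the value per hour stated and varied.
3. Optionally, as a clarification only, state that QALYs will be computed as the area under the EQ-5D-5L curve over the three visits, adjusted for baseline utility.

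Collecting the missing categories instead would be late: under Trial status, 75 of 104 participants (72%) had been recruited by April 2021. The proposed changes need no new data. They cost a few sentences, a small calculation and a narrower economic claim.

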## Methods: monitoring

### Data monitoring

Staff that are providing intervention and collecting parts of the data have been trained in giving the LGO-S intervention by the Swedish Association of Occupational Therapists. To maintain adherence to the trial protocol, interventionists will be gathered for network meetings four times a year, and this will be complemented with visits to the units by the researchers. There is a risk that participants will discontinue treatment or be partially absent from treatment in either treatment arm due to e.g. lack of motivation, lack of time, worsened health or meeting, and travel restrictions due to the COVID-19 pandemic. All deviations from the protocol will be noted by the interventionists. Interim analyses will be performed when 50% of the participants have completed their last assessment. The data collection will stop when the stipulated number of participants is reached or when the principal investigator makes such a decision based on interim analyses. The principal investigator will have the final decision regarding the termination of the trial. No stopping guidelines have been deemed necessary because there are no, or very minor, risks with participation. The extended research group (the authors of this protocol, and in addition two other colleagues) functions as a steering committee that the PI and the project coordinator will report to on a regular basis and also discuss issues with arising during the trial.

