### Sample size

A total of 104 participants will be recruited for the trial. There will be 52 participants in each group. The sample size calculation is based on the earlier feasibility study showing that an increase of 8 ATMS units in mean difference (SD = 10 for both groups) on the time management subscale of the ATMS-S was considered a significant effect [52]. Furthermore, the calculation took into account an 80% power to detect change, a dropout rate of 25%, and a statistical significance level of *p* < 0.01.

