### Statistical analysis plan

#### General statistical considerations

The flow of participants through the study will be illustrated according to the Consolidation Standard of Reporting Trials (CONSORT, Fig. 1) [78].

Prior to data analysis, raw data from each instrument will be coded according to the instructions for the respective instrument. Statistical tests will be two-sided and conducted at the conventional (two-sided) 5% level with no formal adjustment for multiple testing. Secondary outcomes are likely to be highly correlated so that standard adjustment techniques, such as the Bonferroni method, would be conservative [79].

All outcome measures and patient characteristics will be summarised by their trial allocation group and by measurement point. The distribution of outcome data will be examined. The main analysis of outcome data will be the comparison of change from baseline between treatment arms. Change from baseline has a “normalising” effect and standard techniques are generally applicable. To maintain the baseline comparability of the compared groups, the main analyses will be performed on an intention-to-treat basis, meaning that participants will be analysed in the arm they were allocated to. A researcher blinded to group allocation will conduct the statistical analysis, guided by a professional academic statistician (also blinded).

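### The principal investigator may stop the trial on a 50% interim analysis that has no stated scope or boundary, so the two-sided 5% error rate is not controlled

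*Protocol article*

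**What the plan says.** All references are to the protocol article.

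- **Data monitoring, timing:** "Interim analyses will be performed when 50% of the participants have completed their last assessment".
- **Data monitoring, consequence:** data collection ends when the planned number is reached "or when the principal investigator makes such a decision based on interim analyses". The same section gives the principal investigator the last word on termination.
- **Data monitoring, rule:** "No stopping guidelines have been deemed necessary because there are no, or very minor, risks with participation".
- **General statistical considerations:** tests are "conducted at the conventional (two-sided) 5% level with no formal adjustment for multiple testing". The reason given there is that the secondary outcomes are likely to be correlated.
- **Primary outcome analysis:** a t-test or Mann–Whitney test on change from baseline to just after the intervention, with no provision for an interim look.
- **Sample size:** 52 per arm, from "an increase of 8 ATMS units in mean difference (SD = 10 for both groups", "an 80% power to detect change", 25% dropout and "a statistical significance level of *p* < 0.01".

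No section says which outcome the interim examines, whether arms are compared, or on what grounds the trial would stop.

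**The concern.** The article grants a power to stop on interim results and then declines a rule for using it. Low participant risk is a reason to do without a safety boundary. It is no reason to do without an efficacy boundary, whose purpose is to keep the false-positive rate at its stated value when the data may be tested twice.

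This is more than detail left to an analysis plan. A later plan that added a stopping boundary would contradict the statement that none is needed.

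Two things are at stake. If the interim is a comparative look at the primary outcome, a stop on a nominally significant result raises the type I error above 5% and exaggerates the effect. The trial is also open, its outcomes are mostly self-reported, and the stopping decision lies inside the team that runs it. Any between-arm result that became known could affect the rest of recruitment and rating.

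**Working it through.** **1. Reproduce the planned size.** Inputs from Sample size: difference 8, SD 10 (standardised difference 8/10 = 0.8), power 80%, significance level 0.01, dropout 25%. A two-sided two-sample t-test (noncentral t) needs 39 per arm, with power 81.0%. Then 39/(1 − 0.25) = 52 per arm, or 104 in total. This matches the article, so about 2 × 39 = 78 analysable participants are expected at the end.

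**2. Information fraction t at the interim.** The trigger is 50% having completed their last assessment, which is the 3-month visit. The primary endpoint falls earlier, 1–2 weeks after the intervention, so at least that many have primary data.
- If 50% means half of the eventual completers: t = 39/78 = 0.5 or more.
- If 50% means 52 of the 104 recruited: t = 52/78 ≈ 0.67 or more.

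Values below 0.5 do not fit this trigger.

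**3. Type I error, conditional on an assumed rule.** Assume the arms are compared on the primary outcome, the trial stops if p<0.05, and otherwise the final test is at 0.05. Under no effect, the interim and final statistics Z₁ and Z₂ are bivariate normal with correlation √t.

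- Stop in either direction: error = 1 − P(|Z₁| ≤ 1.96 and |Z₂| ≤ 1.96).
- Stop only in favour of LGO-S: error = P(Z₁ > 1.96) + P(Z₁ ≤ 1.96 and |Z₂| > 1.96). By symmetry this is 0.05 plus half the excess in the row's first figure. At t = 0.5: 0.05 + 0.0331/2 = 0.0666.

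| t | Either direction | Only in favour of LGO-S |
|---|---|---|
| 0.5 | 8.3% | 6.7% |
| 0.6 | 8.0% | 6.5% |
| 0.67 | 7.7% | 6.3% |
| 0.8 | 7.1% | 6.0% |

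A simulation of t-tests at 20 and then 39 per arm (400,000 runs) gives 8.2% for the first rule at about t = 0.5.

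**4. Overestimation after a stop.** Simulated t-tests with SD 10 and 20 per arm at the interim, stopping at p<0.05:
- True difference 4 units (an assumption, not a protocol figure): the trial stops about 24% of the time, with a mean estimate near 8, about twice the truth.
- True difference 8 units (the planned value): it stops about 70% of the time, with a mean estimate near 9.6.

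**5. Boundaries that hold the level (t = 0.5).**
- Haybittle-Peto, |Z| > 3.29 (p<0.001) at the interim and 1.96 at the end: overall 5.02%. A final level of 0.0498 gives exactly 5%.
- O'Brien-Fleming, 2.797 then 1.977 (p<0.0052, then p<0.0480): 5.0%.

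**6. Power cost of Haybittle-Peto.** With 39 per arm and a standardised difference of 0.8, final-test power is 93.7% at 0.05 and 93.6% at 0.0498.

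**The case against.** The strongest reply is that the article never says the interim compares arms or that a stop would be for efficacy. The sentences just before it concern absence, COVID-19 restrictions and protocol deviations, so a feasibility look may be meant. A pooled look, or a stop for futility only, adds no type I error. This stands. A reader might infer that the error does exceed 5%, but the document supports only the statement that it is not held at 5% and can reach 7–8%. The reply does not rescue the plan, because the wording allows the comparative version and excludes nothing.

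Four further points:

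- **No adjustment for multiple testing.** A reader might take this as a refusal to adjust for the interim. The reason given concerns correlated secondary outcomes, so it shows no decision about repeated looks. It does fix the 5% level.
- **The 1% level in Sample size.** If 1% applied at both looks, the overall error at t = 0.5 would be about 1.8%, above 1% but below 5%. The article does not present the 1% as an allowance for the interim, and the level set for analysis is 5%. The conflict between the two levels is a separate matter.
- **Blinding.** The statistician and the analysing researcher are blinded to allocation. That does not protect the error rate, since a comparison of coded arms still gives a p-value to act on. It does mean one cannot claim that the principal investigator will see unblinded results. The article is silent on that, so operational bias is a risk and not an established fact.
- **Steering committee.** It consists of the protocol authors and two colleagues, and the final decision stays with the principal investigator. It is not an independent safeguard.

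**Conclusion.** The point holds in conditional form. The article permits a stop on interim results, declines a rule for a reason unrelated to type I error, and sets the tests at two-sided 5%. The error rate of the primary claim is therefore not controlled at 5%.

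The size depends on use. For the information fractions that fit the trigger best (0.5 to about 0.67), it is about 8% if the trial stops at nominal p<0.05 in either direction and 6–7% if it stops only in favour of LGO-S. There is no inflation if the look is non-comparative or can stop only for futility. The figures assume one interim look at the primary outcome, about 78 analysable participants at the end, and an unadjusted final test at 5%.

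It should be settled before any interim result is acted on. Trial status reports 75 of 104 recruited in April 2021, so the interim may be close or past. The article does not say which.

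**What to change.** Replace the sentence that allows a stop based on interim analyses with one of two rules.

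- **(a) No efficacy look.** The interim covers only pooled recruitment, dropout and data completeness. There is no between-arm outcome comparison and no efficacy stop. The final test keeps its full level.
- **(b) Bounded efficacy look.** The trial may stop for efficacy only if the primary comparison gives two-sided p<0.001 (Haybittle-Peto). The final test is at 0.05 (overall about 5.02%), or at 0.0498 if exactly 5% is wanted. The interim result is seen only by someone outside recruitment and data collection.

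In either case, remove low participant risk as the reason for having no efficacy rule. If a between-arm look has already been taken, record its date and what was seen.

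The cost is one paragraph, plus the ethics board and registry notification that the article already foresees for important modifications. Option (a) costs no power. Option (b) costs almost none.
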